**Table 1: Sample size estimation for a range of sensitivity levels**

| Sensitivity point estimate (%) | Relative precision (%) | | | |
| --- | --- | --- | --- | --- |
|  | 5 | 10 | 20 | 50 |
| 80 | 385 | 97 | 25 | 4 |
| 85 | 272 | 68 | 17 | 3 |
| 90 | 171 | 43 | 11 | 2 |
| 95 | 81 | 21 | 6 | 1 |

## Data analysis

Analyses will:

- Determine the sensitivity and specificity of the novel assay to detect naturally acquired LASV-specific antibodies in LF survivors and unexposed controls in oral fluids compared to blood samples
- Describe antibody levels among study participants as a function of time since clinical infection and in relation to original clinical characteristics and potential re-exposure events.
- Investigate characteristics of any apparently unexposed controls found to have positive antibodies

## Dissemination of results

The results of the study will be disseminated through reports, academic papers, and presentations. We will ensure that negative results are also reported. All publications will be open-access. We will also share the results directly with the LASV team at KGH, government of Sierra Leone and other organizations working on LASV. A report will be shared with the Sierra Leone Ethics and Scientific Review Committee.

Survivor participants will not be informed of their individual results as knowledge carries no individual benefit to health or wellbeing. Unexposed controls will be informed if they are found to have positive antibodies and the meaning of this will be explained.

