# Aims and objectives

The aim of this study is:

- To develop and examine the validity of a new assay to measure evidence of LASV infection for use with oral fluids by comparing naturally acquired antibody responses to LASV in oral fluids and blood serum samples from LF survivors and unexposed controls.

The specific objectives are:

1. To complete the development of a novel ELISA to investigate naturally acquired antibody responses LASV infection in non-invasive oral fluid samples
2. To validate this tool and determine its sensitivity and specificity by measurement of LASV-specific antibodies in oral fluids and blood samples from LF survivors and unexposed controls
3. To evaluate the feasibility of oral fluid as an alternative sampling tool using these findings
4. In LF survivors, to correlate LASV-specific antibody responses with time since clinical infection, original clinical characteristics and potential re-exposure events.

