## Sample collection

A 5ml blood sample will be collected and stored in a cool box for daily transfer to the laboratory. Serum will be processed then stored at -20°C prior to testing antibody responses.

Oral fluid will be collected by the participant rubbing a small sponge swab firmly on the gums for 90 seconds, then placing it in a stoppered plastic tube and in a sealable plastic bag and stored in a cool box, then transferred for storage at -20°C at the end of the day prior to testing antibody responses. Experience suggests that oral fluid collection is acceptable to participants of all ages.^18^

Oral fluid and blood samples will be tested to detect anti-LASV antibodies using the new ELISA tool. Further comparative tests may be conducted with assays currently in use in KGH.

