# Human subjects’ protection

## Risks to participants

The study protocol will be submitted to the Sierra Leone Ethics and Scientific Review Committee and at LSHTM for approval. No implementation will begin until approval is received. Written informed consent will be sought as described in section 2.3 above.

There is a risk that participants may not be properly informed about the study. Risks of drawing blood from participants are typically minor, with a bruise at the puncture site being the most common adverse event and a very small risk of infection. There is risk that participants may experience duress during the recruitment and interview process or in providing samples for analysis and a risk of loss of privacy. There are no risks in providing oral fluids.

We will take appropriate measures to minimize these risks to participants by providing clear training, guidance and supervision to members of the study team. We will be sensitive to any breach of confidentiality due to the stigmatizing nature of LASV.^19^ Study data will be managed according to a clear operational protocol, with only authorised research team members having access to de-identified data. We will also minimise risk to participants by engaging staff who have already built a rapport with LF survivors.

There will be no costs to the participant for participating in this research study. All costs related to the study, including phlebotomy and laboratory testing, will be paid for by the study.

Recruitment and participation will require a maximum time commitment of 1 hour from each participant, financial compensation of 100,000 Leones (approximately $11) will be provided for inconvenience, transport and loss of work time. This amount is consistent with the amount paid per follow-up visit by the Survivors Study.

Child survivors will be recruited into the study after the informed consent from their parent or guardian. In accordance with Sierra Leonean age cut-offs for child participation in research, children older than 12 years will also be asked to provide assent to participate. Pregnant women will be eligible to participate in either study cohort.

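### Controls are to be told of positive Lassa antibodies with no required confirmation, on an assay whose specificity is still unknown, so a disclosed positive may well be false

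*Protocol*

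**What the plan says.** Under Dissemination of results the Protocol sets different rules for the two groups. For survivors: "Survivor participants will not be informed of their individual results as knowledge carries no individual benefit to health or wellbeing". For controls: "Unexposed controls will be informed if they are found to have positive antibodies and the meaning of this will be explained". No reason is given for the difference.

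Under Sample collection, one test is committed to: "Oral fluid and blood samples will be tested to detect anti-LASV antibodies using the new ELISA tool". Any other test is optional: "Further comparative tests may be conducted with assays currently in use in KGH". That option is not linked to what controls are told.

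The performance of the new ELISA is an objective of the study (Aims and objectives): "To validate this tool and determine its sensitivity and specificity by measurement of LASV-specific antibodies in oral fluids and blood samples".

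Controls are selected to be free of exposure. Section 4.1 excludes anyone with past Lassa illness or a positive test, anyone who has lived in, worked in or visited an endemic area, and anyone with case contact. Section 4.2 adds a screening questionnaire. The Data analysis section uses both groups to estimate accuracy, and separately plans to "Investigate characteristics of any apparently unexposed controls found to have positive antibodies".

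**The concern.** A test of unknown specificity, applied to people chosen because they should be negative, is the setting in which a positive result is least trustworthy. The controls are nevertheless the group who receive individual results. As written, nothing has to happen between a positive reading and telling the participant: no repeat, no second assay, no rule on which fluid counts, and no wait until the specificity estimate exists.

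At stake is a participant being told of evidence of past Lassa infection when there was none, which cannot easily be undone once said. The Protocol recognises that the disease carries stigma ("We will be sensitive to any breach of confidentiality due to the stigmatizing nature of LASV"), although it does so when discussing confidentiality. Its list of risks does not include the return of a wrong result. The planned look at antibody-positive controls would also mix reproducible positives with one-off readings.

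**Working it through.** **Inputs from the Protocol.**
- Controls: 70 (Sample size).
- Sensitivity: 85%, the planning value (Sample size).
- Specificity of the new assay: no expected value is given. The 61.2% under Sample size is described only as a lower value that could be estimated, so it is not used here.
- Benchmark: section 2.2 reports 99.7% specificity, lower 95% limit 98.4%, for an oral-fluid ELISA for Ebola. That is a different assay.

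**Assumptions.** Specificities of 95% and 90% widen the range. True antibody prevalence among controls is not given; 0% to 5% is shown.

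**The plan's own figure.** The group size rests on Table 1: n = 1.96² × (1 − p) / (p × r²). With p = 0.85 and r = 0.10 this is 67.79, rounded up to 68, as printed. Only the number 70 is carried forward; the point depends on no other sample-size figure.

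**Step 1: false positives if all 70 controls are truly unexposed.** Expected number = 70 × (1 − Sp). Chance of at least one = 1 − Sp^70. Both are per fluid.

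| Specificity | Expected false positives | Chance of at least one |
|---|---|---|
| 99.7% | 70 × 0.003 = 0.2 | 19% |
| 98.4% | 70 × 0.016 = 1.1 | 68% |
| 95% | 70 × 0.05 = 3.5 | 97% |
| 90% | 70 × 0.10 = 7.0 | 99.9% |

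**Step 2: if a positive in either fluid led to disclosure.** With independent errors, expected false positives = 70 × (1 − Sp²): 0.4, 2.2 and 6.8 at 99.7%, 98.4% and 95%. The Protocol does not say that either fluid suffices; this shows what leaving the specimen undefined could mean.

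**Step 3: share of disclosed positives that are false when some controls have truly been infected.** With prevalence π and Se = 0.85, share false = (1 − π)(1 − Sp) / [(1 − π)(1 − Sp) + π × Se]. For example, at Sp = 98.4% and π = 1%: 0.01584 / (0.01584 + 0.0085) = 65%.

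| Specificity | π = 0% | 1% | 2% | 5% |
|---|---|---|---|---|
| 99.7% | 100% | 26% | 15% | 6% |
| 98.4% | 100% | 65% | 48% | 26% |
| 95% | 100% | 85% | 74% | 53% |
| 90% | 100% | 92% | 85% | 69% |

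A positive is more likely false than true when π is below (1 − Sp) / [(1 − Sp) + Se]: about 0.35% at 99.7%, 1.8% at 98.4% and 5.6% at 95%. The 0% column is 100% by construction.

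**The case against.** A reader might infer that the Protocol contradicts itself by counting a control positive as a false positive in the analysis while reporting it to the person as a finding. The text does not go that far. It never calls these results false positives. The phrase "Investigate characteristics of any apparently unexposed controls found to have positive antibodies" leaves room for genuine infection. The accuracy analysis is also worded as oral fluid against blood, so paired blood, and not exposure group, may be the reference. Telling a control about a positive that may be genuine is consistent with investigating it. This objection stands. It does not supply independent confirmation, however: on the committed testing, the blood result comes from the same new ELISA.

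A reader might also infer that participants are likely to receive wrong results. At the only benchmark in the document, 99.7%, the chance of any false positive among 70 controls is 19%; with 1% true prevalence, 74% of positives would be genuine. The stronger claim fails there. It cannot be ruled out either, because the benchmark belongs to another assay and at its own lower limit the chance is 68%.

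The disclosure sentence names no assay, and its place under dissemination is compatible with informing people after specificity is known. The Protocol promises to explain the meaning of a positive, and the consent form and information leaflet, which are not in the available text, may already say that the test is under validation. These points soften the concern. But the available text does not say that the explanation will cover false positives, and no explanation replaces a confirmatory result. The stigma sentence concerns breaches of confidentiality, so it supports the seriousness of the label and no more.

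**Conclusion.** The gap is real but narrow. The Protocol commits to telling controls of positive antibodies without requiring confirmation, and the only committed test has unknown specificity. Any positive so disclosed may well be false. How likely that is depends on specificity and true prevalence, neither of which the Protocol gives. Over 99.7% to 90% specificity, the expected number of false positives per fluid among 70 truly unexposed controls runs from 0.2 to 7.0, and the chance of at least one from 19% to 99.9%.

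That the new ELISA would be the trigger is the natural reading, since no other test is committed to, but it is not stated. Nothing here alters the sensitivity or specificity estimates or the sample size. The consequence falls on individual controls and on the interpretation of the positive-control investigation.

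**What to change.** Reconcile Sample collection, Data analysis and Dissemination of results:

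- State which assay and which specimen define a reportable positive in a control.
- Inform a control only after the specificity analysis is complete and the positive has been reproduced on a repeat run. Where the Kenema hospital has an assay suited to past infection, also require confirmation on the stored serum. That condition matters: section 4.1 names only antigen and IgM ELISAs there, and the Protocol does not show that a suitable assay is in use.
- Run these tests before samples are destroyed for participants who declined storage.
- State that the explanation will include the chance of a false positive.
- Give the reason for treating survivors and controls differently.
- In Data analysis, describe confirmed and unconfirmed control positives separately, leaving the main specificity estimate unchanged.

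The cost is repeat assays on a few samples already held, a few sentences of text, and a later answer for the controls concerned.

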# Human subjects’ protection

## Risks to participants

The study protocol will be submitted to the Sierra Leone Ethics and Scientific Review Committee and at LSHTM for approval. No implementation will begin until approval is received. Written informed consent will be sought as described in section 2.3 above.

There is a risk that participants may not be properly informed about the study. Risks of drawing blood from participants are typically minor, with a bruise at the puncture site being the most common adverse event and a very small risk of infection. There is risk that participants may experience duress during the recruitment and interview process or in providing samples for analysis and a risk of loss of privacy. There are no risks in providing oral fluids.

We will take appropriate measures to minimize these risks to participants by providing clear training, guidance and supervision to members of the study team. We will be sensitive to any breach of confidentiality due to the stigmatizing nature of LASV.^19^ Study data will be managed according to a clear operational protocol, with only authorised research team members having access to de-identified data. We will also minimise risk to participants by engaging staff who have already built a rapport with LF survivors.

There will be no costs to the participant for participating in this research study. All costs related to the study, including phlebotomy and laboratory testing, will be paid for by the study.

Recruitment and participation will require a maximum time commitment of 1 hour from each participant, financial compensation of 100,000 Leones (approximately $11) will be provided for inconvenience, transport and loss of work time. This amount is consistent with the amount paid per follow-up visit by the Survivors Study.

Child survivors will be recruited into the study after the informed consent from their parent or guardian. In accordance with Sierra Leonean age cut-offs for child participation in research, children older than 12 years will also be asked to provide assent to participate. Pregnant women will be eligible to participate in either study cohort.

Participants will be informed that participation is voluntary and that they are free to discontinue their participation at any time with no adverse consequence. As the primary aim of this work is to validate an assay, individuals who do not wish to provide any oral fluid and/or blood samples will not be recruited. Participation in, or discontinuation from the study will not affect the participant’s ability to receive medical care provided by the Sierra Leone health service. The study will not offer or provide any medical care, other than to respond to an emergency unexpected reaction to the sampling procedure.

## Intellectual property

Participants will be informed that the researchers and study team will not benefit financially from the development and testing of this assay. No intellectual property rights (IPR) will be sought for the new assay, and IPR linked to the conjugate component of the assay will be waived for production of the assay by state laboratories in endemic countries. Sample donors will be asked to freely donate a single blood and oral fluid sample and to relinquish all rights, title and interest to these samples.

## Data handling

Maintaining participant confidentiality is an essential part of medical research. Staff will receive training on ensuring patient confidentiality, and all data collected on study participants will be secured (locked if paper or password-protected/encrypted if electronic). All participants will be assigned a unique identifying number. An electronic file as well as a paper log book will be kept by the study coordinator linking patient names with the unique identifying number. All electronic master lists will be kept on password-protected computers in locked offices or in the restricted access laboratory in the Lassa unit. Paper log books will be kept in a locked cabinet in locked offices. All electronic copies of medical records and laboratory documents will be kept on password-protected computers in locked offices with restricted access.

An anonymised version of the raw database(s) stripped of all identifying information such as participant name, address, etc. will be created for analysis. Only authorised members of the LSHTM and Lassa Fever Unit data team will have access to the raw data including the personal identifiers, and only for the purpose of entering the information into an electronic database, checking for errors, and producing the anonymised version of the database for analysis at LSHTM. The electronic database will be password-protected and stored on a secure server owned by the London School of Hygiene & Tropical Medicine.

De-identified data will be shared with KGH investigators. No individual data or samples will be sold to or shared with third parties beyond the collaboration.

## Storage of study participants’ samples

Study participants will be asked to consent to allowing any residual samples to be stored for future testing and given the option to refuse. Participants who change their mind regarding storage of their samples may contact a study investigator at any time to request that their samples be destroyed. Future use of specimens by other investigators and collaborators will be limited to their receipt as anonymized samples.

**c) Study Questionnaire**

**STUDY CHECKLIST**

| **Tick/date/initial as required when task/document is completed** | | **Notes** |
| --- | --- | --- |
| Participant ID No.: (write number) | # |  |
| Date of Visit: | dd - mmm - yyyy |  |
| Eligibility Verified | initial |  |
| Consent Form Completed | initial |  |
| Temperature recorded | initial |  |
| Questionnaire Completed | initial |  |
| Oral Fluid Collection Completed | initial |  |
| Blood Collection Completed | initial |  |
| Samples received by Study Coordinator | initial |  |
| Entered into Enrolment Log | initial |  |
| Entered into Database | dd - mmm – yyyy  initial |  |

**SURVIVOR PARTICIPANT QUESTIONNAIRE**

| **Temperature (°C)** | **If above 37.9°C, postpone sampling and recommend to visit a doctor** |
| --- | --- |

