# Methods

## 4.1 Recruitment

**Inclusion Criteria**

For LF survivor participants

- History of LF as documented by a positive anti-LASV Ag or IgM ELISA in the KGH diagnostic laboratory
- Age ≥6 years
- No fever at recruitment (Temperature below 37.5^o^C)
- Willingness to provide informed consent (or assent, if applicable)
- Willingness to undergo phlebotomy for blood samples and provide oral fluid samples

For unexposed control participants

- No history of LF clinical illness and/or LASV positive test,
- No history of residence, work or visiting in LF endemic zones
- No history of contact with a LF case
- Age ≥6 years
- No fever at recruitment (Temperature below 37.5^o^C)
- Willingness to provide informed consent (or assent, if applicable)
- Willingness to undergo phlebotomy for blood samples and provide oral fluid samples

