## 4.4 Eligibility & consent

After holding meetings with key community leaders and Lassa survivor communities about the aims of the study, individual survivors will be approached for recruitment. The purpose and objectives of the study will be explained verbally, and a patient information leaflet provided for those able to read (Appendix 3: Patient information leaflet). Study investigators will explain the role of the participant in the study and discuss potential risks of participation. Informed consent will be in English. If English is not the patient’s native language or they are unable to read, the patient will be informed about the study and related risks in his or her native language by a collaborating investigator fluent in that language who will read the consent form to the potential participant in the presence of a witness.

Potential participants will have the opportunity to raise any concerns, after which, written informed consent will be sought from all adult participants and from adult guardians of child participants (Appendix 1: Consent form). For survivors, consent will include approval to access clinical records of their LF admission and to information previously given to the Survivors Study. All participants will be asked to consent to storage of their oral fluid and blood samples for possible future research; samples from participants who do not agree to storage will be destroyed after the validation study.

Following provision of informed consent, clinical, demographic and risk factor information for the participant will be collected from medical records completed during admission and from the Survivor Study database. Participants will be asked to respond to a short questionnaire specific to the validation study focussing on possible antibody-boosting exposures (Appendix 2: Questionnaires). Data will be entered into a password-protected electronic database.

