## Data collection

Data will be collected using a study-specific questionnaire (Appendix 2), participants’ medical records during admission to KGH Lassa Fever Unit, and data held in the Survivors Study database. Variables for survivors will include demographics, symptoms and clinical information at the time of admission, dates of LF onset and discharge, laboratory test results at discharge, and information on any known exposure to LASV or LF patients since recovery, in order to explore potential immunity-boosting events.

Unexposed participants will be asked a series of questions regarding exposure to LASV hosts and/or cases to determine if they fulfil the inclusion criteria, and if not excluded based on responses, will be asked to respond to a brief demographic questionnaire.

Both groups will be asked to give feedback on using the oral fluid swab, including perceptions of the method as a follow-up and research tool.

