**CONTROL PARTICIPANT ELIGIBILITY CHECK**

**For ‘Not eligible’ responses: do not recruit into the study; no further questions, no sample collection.**

| **Were you ever tested for Lassa Fever?** (circle one) **Yes No** | |
| --- | --- |
| **What was the final result of your test for Lassa Fever?** (circle one)  **Negative**  **Didn’t receive result (Not eligible) Don’t remember (Not eligible) Positive (Not eligible)** | |
| **Have you ever lived, worked or visited in a Lassa-endemic area? Yes (Not eligible) No** | |
| **Has anyone within your household had Lassa Fever? Yes (Not eligible) No** | |
| **Do you know anyone outside your household who got Lassa Fever? Yes No** | |
| **If Yes, did you have contact with them? Yes (Not eligible) No** | |
| **Temperature: (°C)** | **If above 37.5°C – Not eligible for study participation, no further questions and no sample collection. Advise individual to seek medical advice** |

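### The survivor form stops sampling only above 37.9°C, but the inclusion criterion requires a temperature below 37.5°C, so ineligible survivors could be sampled

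*Protocol*

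**What the plan says.** The Inclusion Criteria in Protocol section 4.1 print the same line in the survivor list and in the control list: "No fever at recruitment (Temperature below 37.5^o^C"). The limit is strict, so a reading of exactly 37.5°C fails.

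Two forms in the appendix turn temperature into an instruction for staff:

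- The survivor participant questionnaire: "If above 37.9°C, postpone sampling and recommend to visit a doctor".
- The control participant eligibility check: "If above 37.5°C – Not eligible for study participation, no further questions and no sample collection".

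The study checklist has a row to be initialled, "Eligibility Verified", which shows no temperature limit. The row for recording temperature comes later in the same list. The Data collection section describes screening questions "to determine if they fulfil the inclusion criteria" for unexposed participants only, and names no equivalent step for survivors.

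**The concern.** The inclusion criterion and the form meant to apply it give different answers for the same person. In the pages available, 37.9°C is the only temperature limit that a survivor interviewer sees. An interviewer who works from the form would go ahead with someone at 37.7°C, although section 4.1 excludes that person.

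What is at stake is adherence to eligibility. Each survivor sampled in the gap is an eligibility deviation. The criterion is also meant to be common to both groups, yet the forms apply it unequally: between 37.6 and 37.9°C a control is turned away and a survivor is sampled.

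**Working it through.** No statistical formula applies. The check compares the three limits as rules on a temperature T. It assumes readings to one decimal, the precision in which the Protocol prints its limits.

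**Inputs**

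| Source | Rule as written | Consequence |
| --- | --- | --- |
| Section 4.1, both groups | T < 37.5 | eligible on temperature |
| Survivor questionnaire | T > 37.9 | sampling postponed |
| Control eligibility check | T > 37.5 | not eligible |

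**Survivors.** A reading slips through if it fails section 4.1 (T ≥ 37.5) and does not trigger the form (T ≤ 37.9). Together these give 37.5 ≤ T ≤ 37.9. The width is 37.9 − 37.5 = 0.4°C. The one-decimal readings are 37.5, 37.6, 37.7, 37.8 and 37.9, which is five values.

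**Controls.** A reading slips through if T ≥ 37.5 and T ≤ 37.5, so only at exactly 37.5. Apart from that one boundary value, the control form uses the criterion's own number.

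**Between groups.** Readings at which the control form refuses and the survivor form proceeds satisfy T > 37.5 and T ≤ 37.9: 37.6, 37.7, 37.8 and 37.9, which is four values.

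**Could 37.9°C be a deliberate second limit?** A separate stop for sampling would need to act on someone whom the eligibility rule had let through. Anyone with T > 37.9 already has T ≥ 37.5 and is already excluded. With section 4.1 in force, the 37.9°C limit therefore stops nobody who is not already stopped.

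**After the change.** With T ≥ 37.5 as the trigger on both forms, a reading that fails section 4.1 and is not stopped would need T ≥ 37.5 and T < 37.5. No such reading exists.

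**The case against.** The strongest reply is that the two limits govern different acts. Section 4.1 decides eligibility at recruitment, whereas the survivor form only postpones sampling and nowhere says that people up to 37.9°C are eligible. The control form, by contrast, does speak of eligibility. On this reading the inclusion criterion stays in force and the initialled eligibility row on the checklist applies it. The Protocol also promises staff training and supervision. Staff who check against section 4.1 would stop at 37.5°C whatever the survivor form says.

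Part of this stands. Sampling in the gap is possible, not certain, and depends on staff relying on the form. The checklist safeguard is incomplete, however: its eligibility row shows no limit and is listed before the temperature row. Nor does the second-limit reading explain 37.9°C, because a looser limit behind a stricter one has no work to do.

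Three smaller objections are fair:

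- Section 4.1 does not require referral to a doctor at 37.5°C, so a missed referral in the gap follows from the form's wording but breaches nothing in the body of the Protocol.
- The Protocol links no antibody result to a recruitment temperature in this range.
- The questionnaire pages shown begin at item c) of the appendix, so a survivor eligibility form on an unseen page cannot be ruled out. Such a form could reduce the practical risk, but the questionnaire would still contradict section 4.1.

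**Conclusion.** The contradiction is real and the text is wrong as written. A survivor reading of 37.5 to 37.9°C, a band of 0.4°C, fails the inclusion criterion without triggering the survivor form. The mismatch itself needs no assumption beyond the printed limits. The practical consequence assumes that staff act on the form in front of them and that no other survivor form shows 37.5°C.

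The consequence is modest: eligibility deviations of unknown number, with no claim about the accuracy estimates or their precision. It is still worth correcting, because it is a wrong decision threshold on a working form and almost free to put right.

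**What to change.** 1. On the survivor questionnaire, change the trigger from above 37.9°C to 37.5°C or above, and leave the rest of the instruction unchanged.
2. On the control eligibility check, change above 37.5°C to 37.5°C or above, which closes the single boundary reading.
3. Leave the criterion in section 4.1 as it is.

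The checklist does not have to change. If it is reordered anyway, move the eligibility row below the temperature row, so that consent still precedes data collection as section 4.4 requires ("Following provision of informed consent, clinical, demographic and risk factor information for the participant will be collected").

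The cost is one line on one form and one phrase on another, with no change to a criterion, the sample size or the analysis. The Risks to participants section describes ethics submission as still to come ("The study protocol will be submitted to the Sierra Leone Ethics and Scientific Review Committee and at LSHTM for approval"), so the corrected forms can go in with the Protocol. If approval has already been given, the two corrected pages would have to go to both bodies.
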